##### 2.5.1.3 Basic treatment and medication changes

During the baseline period, all details of medications used by the patients to treat COPD and other underlying conditions will be recorded on a case report form (CRF), including the name of the medication, the dosage used, the frequency of use, the route of administration, and when the medications begin and end. Any changes in the patient’s medications throughout the study period will also be recorded in detail. If the patient experiences an acute exacerbation, the possibility of continuing acupuncture treatment will be assessed by a respiratory medicine specialist. If an acute exacerbation occurs that necessitates the application of antibiotics or hospitalization to control the infection, the trial will be discontinued and the time and reason for being discontinued will be recorded by the investigators.

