### 2.10 Statistical analysis

Analyses of effectiveness, indicators of DNA library of gut microbiota, content of metabolites, percentage of immune cell and expression levels of inflammatory cytokines will be performed according to the Per Protocol Set (PPS) principle. The missing data will be filled in by multiple interpolation. SPSS 27.0 software (IBM Corp, New York) will be applied for statistical analysis. Quantitative indicators will be described by mean value (± standard deviation) or median (± interquartile range), and classification indicators by frequency and percentage. Baseline data will be analyzed using Chi-square or Fisher precision tests (data with frequency less than 5) and ANOVA. Sensitivity analyses will be performed using ANOVA.

The outcome of effectiveness, indicators of DNA library of gut microbiota, content of metabolites, percentage of immune cell and expression levels of inflammatory cytokines will be analyzed by linear mixed effects model. Fixed effects will be set for analyzing groups, COPD subtypes and smoking index (calculation method: smoking years × daily smoking number ÷20); Random effects for sub-centers and baseline outcome measures, both including intercept; Model-based covariance will be applied to test the fixed effects and coefficients, the degree of freedom will use residual method, and the maximum number of iterations will be set to 100. To control for type I error rates under multiple comparisons, the Benjamini–Hochberg method will be utilized for multiple comparison correction. Multiple linear regression will be used to analyze the relationship between clinical efficacy and gut microbiota, metabolites, immune cells and inflammatory factors. Statistical tests will be bilateral with *P* < 0.05 considered statistically significant.

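### The only sensitivity analysis named, an ANOVA, varies the model form and leaves the Per Protocol Set and the imputation behind the week-12 CAT result unexamined

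*Protocol article*

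**What the plan says.** All references are to the protocol article.

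- **Sensitivity analysis (2.10):** one sentence, "Sensitivity analyses will be performed using ANOVA". It gives no response variable, covariates, analysis set or handling of missing values.
- **Main analysis (2.10):** a linear mixed effects model. "Fixed effects will be set for analyzing groups, COPD subtypes and smoking index"; "Random effects for sub-centers and baseline outcome measures, both including intercept".
- **Analysis set (2.10):** the effectiveness analyses "will be performed according to the Per Protocol Set (PPS) principle". No analysis of all randomized patients is named.
- **Missing data (2.10):** "The missing data will be filled in by multiple interpolation", evidently multiple imputation. No departure from its usual assumption is named.
- **Discontinuation (2.5.1.3):** "If an acute exacerbation occurs that necessitates the application of antibiotics or hospitalization to control the infection, the trial will be discontinued".
- **Follow-up after stopping (2.7):** participants who abort are still to be followed, with results recorded.
- **Primary outcome (2.6.1):** change in CAT from week 0 to week 12.

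**The concern.** A sensitivity analysis is useful when it alters an assumption that could be wrong and could move the result. Here the vulnerable step is deciding whose week-12 CAT counts, and what value stands in for a missing one. Under section 2.5.1.3, patients who worsen in a particular way leave the trial. CAT measures the burden of the same disease, so leaving is related to the outcome.

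Such patients can drop out of the result by two routes. They may be excluded from the Per Protocol Set before any imputation takes place. Or they may stay in the set with a missing score that is imputed as if they resembled similar patients who remained. As described, ANOVA addresses neither route. If both analyses use the same patients and the same filled-in values, they share any bias and will tend to agree. A reader could then take that agreement as evidence of robustness that it does not provide.

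**Working it through.** **1. The plan's own figures (2.4.1).** Mean CAT change 5.0 versus 1.4, difference 3.6; two-sided alpha 0.05; power 80%; 32 per group before dropout. The dropout step reproduces: 32 / 0.9 = 35.6, so 36 per group and 72 in total. The 32 cannot be reproduced because no SD is given. Solving the two-group t-test (or F-test) for 80% power at n = 32 gives an SD of 5.06; 5.05 is used below.

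**2. What each analysis varies.**

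| Choice | Mixed model | ANOVA, as written |
|---|---|---|
| Model form | group, subtype, smoking index; random center and baseline | simpler, details not stated |
| Analysis set | Per Protocol Set | no other set named |
| Missing data | multiple imputation | no other method named |

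Only the first row is stated to differ.

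**3. How much loss the discontinuation rule could produce.** Table 2 requires at least one moderate or severe exacerbation in the past year; the list in 2.3.2.1 omits this criterion. The on-study rate is not given. Assuming a constant rate of qualifying events, the share with at least one in 12 weeks is 1 − exp(−rate × 12/52):

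- 0.5 per year: 1 − exp(−0.115) = 11%
- 1 per year: 1 − exp(−0.231) = 21%

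The plan allows for 10%. Not every moderate or severe event triggers the rule (one treated with oral corticosteroids alone would not), so the rate to use is that of events needing antibiotics or hospitalization.

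**4. How far the estimate moves.** Let p be the fraction missing and δ the number of CAT points by which those patients are worse than imputed. The difference then falls by p(MA) × δ(MA) − p(SA) × δ(SA). The same arithmetic covers exclusion, with δ measured against the patients kept. Illustration: 20% lost in one arm, 8% in the other, δ = 5 in both. The shift is (0.20 − 0.08) × 5 = 0.6, so the true difference is 3.0 or 4.2 while an analysis on the imputed values centers on 3.6.

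**5. Tipping point.** With 36 per group:

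- SE = 5.05 × √(2/36) = 1.19
- Smallest significant difference = 1.99 × 1.19 = 2.37 (70 df)
- Shift needed in acupuncture values only = (observed difference − 2.37) / p

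| Observed difference | 10% missing | 20% missing | 30% missing |
|---|---|---|---|
| 3.6 | 12.3 | 6.1 | 4.1 |
| 2.8 | 4.3 | 2.1 | 1.4 |

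This holds the SE fixed and ignores imputation variance and covariate adjustment. The observed 2.8, the loss fractions and the shift in one arm only are assumptions.

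**The case against.** **ANOVA does have a use.** The main model treats the baseline outcome as a random effect and has only four centers. That specification is unusual, and a simpler analysis shows whether the result depends on it. The sample size was also computed with an ANOVA module. This stands: it would be wrong to say that ANOVA tests nothing doubtful.

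**The ANOVA's data set is not stated.** A reader might infer that it reuses the same imputed values and so must reproduce their bias. Section 2.10 does not say so, and different handling is not excluded. Missing at random is likewise the usual assumption of imputation, not one the article states.

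**A failed ANOVA need not mislead.** A reader might infer that ANOVA will often contradict a true positive because it discards baseline information. In simulation at the planned effect, ANOVA of change was non-significant in about 6% to 15% of trials in which a baseline-adjusted model was significant, for assumed correlations from 0.8 down to 0.3. The comparator was a generic baseline-adjusted model, not the planned one, so the gain in precision under the actual plan is unknown. That rate is also modest.

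**The planned effect is fairly safe.** In the 20%/8% illustration, loss averages 14%, above the planned 10%. The worse case of 3.0 still gives t = 3.0 / (5.06 × √(2/32)) = 3.0 / 1.265 = 2.37, p about 0.02. At 10% loss and the full effect, a 12-point shift is large on a 0 to 40 scale. A reader should not infer that missing data alone would probably overturn such a result. The margin is thin only for a smaller observed effect or heavier loss.

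**Follow-up and scope.** Section 2.7 promises follow-up of those who abort. It sits under safety, so its reach to week-12 CAT after an exacerbation is unclear, but some scores may be observed. The shift parameters could properly be left to an analysis plan that is not shown. Neither point makes ANOVA the right tool for the purpose the article assigns it.

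**Conclusion.** The point holds in limited form. The article fixes ANOVA as its sensitivity analysis, and as described this checks model form only. The Per Protocol Set and the imputation go unexamined, although the discontinuation rule links both to worsening disease. Agreement between the two analyses gives no assurance about patients who leave after an exacerbation.

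The consequence ranges from small to material. The tipping shift is about 12 CAT points with 10% missing and a 3.6-point difference, about 6 with 20% missing, and 4 or less if the observed difference is 2.8. These figures rest on the back-solved SD of about 5.05, 36 per group, a fixed SE and assumed loss. The documents do not show that the primary result will be biased or reversed. They show that the one check named could not reveal it. This should be changed; it does not invalidate the design.

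**What to change.** Replace the sentence in section 2.10. The sensitivity analysis for week-12 CAT should:

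1. Repeat the primary model in all randomized COPD patients. Repeating it in the Per Protocol Set could still leave out those who discontinue.
2. Use CAT scores observed after discontinuation where they exist, and state that the follow-up in section 2.7 includes them.
3. Impute the remainder with delta adjustment, making imputed scores worse in each arm separately and in both jointly.
4. Cover a range wide enough to reach and report the tipping point. At the planned effect and 10% missing, this means beyond about 12 points; a range ending at 8 would not reach it.

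Keep ANOVA as an unadjusted check of model form, and state its response variable and data set.

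The cost is protocol or analysis-plan wording and a few extra runs. No new visit is needed, since week-12 CAT is already scheduled. The primary result may look less robust than it would with ANOVA alone.

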**Assessments**								
CAT		×	×	×	×	×	×	
mMRC		×	×	×	×	×	×	
SGRQ		×	×	×	×	×	×	
6-MWT		×			×	×	×	
Times of AECOPD						×	×	
Blinding assessment					×			
Safety assessment			×	×	×			
Adherence evaluation		×	×	×	×	×	×	

COPD, chronic obstructive pulmonary disease; CAT, COPD Assessment Test; mMRC, modified Medical Research Council; SGRQ, St. George’s Respiratory Questionnaire; 6MWT, 6-min walk test; AECOPD, acute exacerbation of chronic obstructive pulmonary disease.

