#### 2.6.2 Secondary outcomes

##### 2.6.2.1 Indicators reflecting clinical symptoms

(1) Modified Medical Research Council (mMRC): The mMRC scale will be applied to assess the dyspnea status of COPD patients. The scale is categorized into five grades (0 to 4) according to the level of activity taken when the dyspnea happens, with grade 0 (the least severe) indicating that the patient experienced dyspnea only during strenuous exercise, and grade 4 (the most severe) indicating that the patient experienced dyspnea with just the slightest activity (48).

(2) St. George’s Respiratory Questionnaire (SGRQ): The SGRQ will be applied to assess the life quality of COPD patients. The scale consists of two parts, reflecting the impact of COPD on patients from three dimensions: the first part contains symptomatic questions, answered in the form of single-choice questions, which ask patients about the frequency and severity of the occurrence of cough, sputum, shortness of breath, and dyspnea; the second part is based on right and wrong questions, which include questions about activities (activity limitation due to dyspnea) and the impact of the disease (impaired socialization and psychological disorders due to airway disease). The 3 main dimensions is scored according to the weighting of the different questions, with the scores calculated using a weighted average method, resulting in a symptom score, an activity score, and an impact score, which are finally summarized to give a total score. Higher patient scores indicate poorer quality of life (49).

(3) 6-min walk test (6MWT): The 6MWT will be applied to assess the exercise tolerance of COPD patients. The test is commonly used to objectively assess patients with moderate-to-severe pulmonary disease. In the test, patients will be asked to walk as far as they can for 6 min along a 30-meter-long corridor. The 6-min walk distance (6MWD) (50), heart rate, respiratory rate, and the values of oxygen saturation (SpO_2_) will be recorded before and after the test (51). The degree of dyspnea will be assessed before and after the test by the Borg scale. The Borg scale consists of a magnitude of 0–10, with 0 being “no dyspnea at all” and 10 being the “the worst dyspnea.” In conjunction with 6MWD recordings, changes in dyspnea levels at rest and after sub-extreme exercise can be assessed, as well as the patient’s exercise tolerance under daily physical activity.

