(4) Number of moderate or severe acute exacerbations of during the follow-up period: The number of moderate or severe acute exacerbations in the follow-up period will be counted, as one of the indicators for assessing the long-term effects of acupuncture-assisted treatment for COPD.

The moderate (patient needs to be treated with short acting bronchodilators plus antibiotics and/or oral corticosteroids) and severe (patient requires hospitalization or visits the emergency room) acute exacerbations of COPD are defined and classified referring to the *Global Strategy for the Diagnosis, Management, and Prevention of Chronic Obstructive Lung Disease: the GOLD science committee report 2022* (41).

The measurement nodes for the outcome indicators above are detailed in Table 1.

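### The exacerbation count is sent to the common linear mixed model, which expects a baseline value that is not scheduled for it and ignores time at risk; if follow-up differs by arm, this can create or hide a difference

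*Protocol article*

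**What the plan says.** Section 2.10 opens its model paragraph with "The outcome of effectiveness, indicators of DNA library of gut microbiota, content of metabolites" and assigns the whole list to a linear mixed effects model: "percentage of immune cell and expression levels of inflammatory cytokines will be analyzed by linear mixed effects model". It then fixes the terms: "Fixed effects will be set for analyzing groups, COPD subtypes and smoking index", and "Random effects for sub-centers and baseline outcome measures, both including intercept". It names no rate, offset or follow-up time, and no other model for any clinical outcome.

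Section 2.6.2.1, item (4), makes exacerbations one of those outcomes: "The number of moderate or severe acute exacerbations in the follow-up period will be counted, as one of the indicators for assessing the long-term effects". In Table 1 the row "Times of AECOPD" is marked at weeks 38 and 64 and nowhere else.

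Three other provisions bear on how long a patient is observed:
- Section 2.5.1.3 discontinues the trial when an exacerbation needs antibiotics or admission, and has the time and reason recorded.
- Section 2.7 says that participants who abort are still followed up.
- Section 2.10 uses the per protocol set and fills missing data by multiple imputation.

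**The concern.** A count of events over a period depends on the length of that period. Under the stated model, a patient seen for 10 weeks without an event and one seen for 52 weeks without an event both contribute zero if their counts enter as recorded. If one arm is observed for less time, its mean count falls for that reason alone. Less follow-up in the sham arm hides a real benefit of acupuncture; less follow-up in the acupuncture arm exaggerates one.

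Unequal follow-up is possible here because the discontinuation trigger in section 2.5.1.3 overlaps the event being counted: item (4) defines a moderate exacerbation partly by antibiotic use and a severe one partly by admission. Leaving can therefore depend on the outcome, and so on treatment.

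The baseline term is a second gap. CAT, mMRC, SGRQ and the 6-minute walk test all have a week 0 value in Table 1. The exacerbation count has none, and the protocol does not say what stands in for it.

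The outcome carries weight in the article. The Discussion presents preventing exacerbations as a main reason for treating in the stable phase and justifies the one-year follow-up partly by this count.

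**Working it through.** **The plan's own figure.** Section 2.4.1 has 32 per group and 10% dropout: 32 / (1 − 0.10) = 35.6, rounded up to 36, as stated. No SD is given, so the 32 itself cannot be checked. The point does not depend on it; 32 per arm is used below as the evaluable number.

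**Does the model fit the outcome?**

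| Model element in 2.10 | What the protocol provides for the count |
|---|---|
| Baseline value of the outcome | No week 0 mark in Table 1. Table 2 requires at least one event in the past year, but the protocol does not name a prior-year count as the baseline |
| Exposure | No term, although section 2.5.1.3 has the time of discontinuation recorded |
| Gaussian response | A small, skewed, non-negative count |

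**Size of the effect. Assumptions, none of them in the documents:** 1.5 events per year in the sham arm, negative binomial dispersion k = 1, 32 per arm, and a fraction q of an arm leaving at a uniformly distributed time in the year. A two-sample t-test on raw counts stands in for the group effect of the linear model.

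Mean follow-up in an arm is 1 − q/2 years, so the expected raw count is rate × (1 − q/2). For q = 0.10 and 0.30 in the sham arm this gives 1.5 × 0.95 = 1.425 and 1.5 × 0.85 = 1.275.

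| True effect | Early exit, acupuncture / sham | Expected counts | Ratio of raw means | Rejection rate |
|---|---|---|---|---|
| None | 0% / 10% | 1.5 / 1.425 | 1.05 | about 5% |
| None | 0% / 30% | 1.5 / 1.275 | 1.18 | about 7% |
| Halving | 0% / 0% | 0.75 / 1.5 | 0.50 | 47% |
| Halving | 10% / 10% | 0.7125 / 1.425 | 0.50 | 44% |
| Halving | 0% / 10% | 0.75 / 1.425 | 0.53 | 40% |
| Halving | 0% / 30% | 0.75 / 1.275 | 0.59 | 26% |

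The t-test rates come from long simulations (20,000 to 40,000 trials). A negative binomial model with log follow-up time as offset has about 50% power for the halving. Under the null it rejects about 6 to 8% of the time in 600 runs, with a standard error near 1 point (√(0.06 × 0.94 / 600) = 0.0097), so part of its apparent advantage is a slightly liberal test.

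**Other assumptions, same direction.** With sham rate 1.0 per year, dispersion 0.5 and 10% exit in the acupuncture arm:
- Equal rates: 30% or 50% exit in sham gives a spurious difference of 0.95 − 0.85 = 0.10 or 0.95 − 0.75 = 0.20 events, and type I error of 6.2% or 10.6%. With 10% exit in both arms it is 4.9%.
- True rates 0.6 and 1.0: the difference is −0.40 (power 31%) with full follow-up in both arms, 0.57 − 0.85 = −0.28 (18%) with 30% exit in sham, and 0.57 − 0.75 = −0.18 (10%) with 50%. Events per person-year give a ratio of 0.59 to 0.60 throughout.
- If counting stopped at each patient's first event, the difference for 0.6 against 1.0 would shrink from −0.40 to −0.15 and power from 31% to 24%.

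**The case against.** The strongest reply is that the protocol gives no sign of unequal follow-up. Patients are blinded, both arms have the same visits and the same one-year window, those who abort are still followed under section 2.7, and missing values are imputed. Section 2.4.1 allows for at most 10% dropout, and at that level type I error stays at about 5%.

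Much of this stands. A reader might infer that the linear model is biased for this outcome whatever happens. The documents do not support that: with equal follow-up it is unbiased, and the power cost against the count model is small (47% against about 50%). The safeguards soften the risk but do not remove it:
- Sections 2.5.1.3 and 2.7 leave open whether a patient discontinued for an exacerbation is still observed.
- Multiple imputation is not specified for a count observed over part of a period.
- If the per protocol set drops early leavers, it replaces the exposure problem with selection that may depend on the outcome.
- The 10% allowance belongs to a sample size set for week 12; the count runs to week 64.

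A reader might also infer that the model cannot be fitted to this outcome at all. That goes too far. Prior-year exacerbations are assessed for eligibility in Table 2 (though that criterion is absent from the list in the text of section 2.3.2.1), and disease history is taken at week 0. A baseline could come from there; the protocol does not name it.

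Nor does the point extend to mMRC. Five ordered grades in a linear model are open to debate, but no consequence has been shown, and the choice is defensible.

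Finally, a condensed article may leave detail to an analysis plan. Here, however, section 2.10 itself fixes the model, its terms, the degrees-of-freedom method and the iteration limit for all effectiveness outcomes. This is a stated method that does not suit one named outcome.

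**Conclusion.** The point holds in a conditional form. The prescribed model has a baseline term with no scheduled value for the exacerbation count, and it ignores time at risk. The harm depends on follow-up differing between arms. At 10% exit in one arm, type I error is essentially unaffected and power for a halving drops by 7 points (47% to 40%). At 30% in one arm, type I error is about 7% and power drops by 21 points (47% to 26%). These figures rest on assumed rates, dispersion and exit patterns and on a t-test as stand-in for the mixed model, so they show direction and rough size only.

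It should be changed, because the outcome supports the long-term efficacy claim and a better method is cheap. The primary CAT analysis is not affected.

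**What to change.** In section 2.10, take the exacerbation count out of the linear mixed model. Analyse it by negative binomial regression with the log of each patient's time under observation from week 12 as offset, and with group, centre and prior-year exacerbation count as covariates. Report the rate ratio with its confidence interval. Keep the linear model for the other clinical scores.

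Reconcile sections 2.5.1.3 and 2.7 so that it is clear whether patients discontinued for an exacerbation remain under observation and until when. The offset corrects for differing observation time, but not for leaving that predicts later events, so this clarification matters under either model.

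The cost is a change of wording before unblinding. It must be confirmed that the case report form records the number of prior-year exacerbations, not only that there was at least one, and the end of observation for each patient. The one statistical downside is that the negative binomial test is slightly liberal at about 32 per arm, which should be acknowledged when the result is read.

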### 2.2 Trial design and setting

This is a prospective, parallel-controlled, multicenter, randomized controlled trial with blinded participants, outcome assessors, and statistician. A total of 72 COPD patients eligible will be randomly assigned to the manual acupuncture (MA) group and sham acupuncture (SA) group in a 1:1 ratio. The entire study period consists of 1 week of screening, 12 weeks of treatment and 52 weeks of follow-up. Both groups of patients will be assessed on the relevant scales throughout the study cycle (including at the time of enrollment, during the intervention period and the follow-up period), and changes in the clinical symptoms of COPD patients will be observed to clarify the effect of acupuncture on COPD. Furthermore, 36 healthy volunteers will also be recruited as a normal control group and will not receive any treatment. The trial will be conducted in four sub-centers: the Affiliated Hospital of Chengdu University of Traditional Chinese Medicine, the Sichuan Provincial People’s Hospital, the Chengdu Second People’s Hospital, and the Meishan Hospital of Traditional Chinese Medicine.

The study protocol is developed following The Consolidated Standards of Reporting Trials (CONSORT) Framework (38) and The Standards for Reporting Interventions in Clinical Trials of Acupuncture (STRICTA) (39), and will be reported in accordance with the Standard Protocol Items: Recommendations for Interventional Trials (SPIRIT) guidelines and checklist (40). The flow chart of trial procedures is shown in Figure 1, and the study schedule is depicted in Table 1.

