### 2.4 Sample size, randomization and blinding

#### 2.4.1 Sample size calculation

The primary outcome for this study is the change in the COPD Assessment Test (CAT) scores before (week 0) and after (week 12) the intervention. Sample size calculation is based on the results of our pilot trial, which showed a mean change in CAT scores of 5.0 for patients in the acupuncture group and 1.4 in the sham acupuncture group. Using a two-tailed test with type I error of 0.05 and power of 80%, a sample size of 32 cases per group is calculated with a maximum of 10% of participants allowed to drop out or disengage, for a required sample size of 36 cases per group, and a total of 72 participants will be included. Furthermore, 36 healthy participants will be included. The sample size calculation was completed in PASS 15.0 with One-Way Analysis of Variance (ANOVA) F-Tests module.

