### 2.6 Outcome measurements

#### 2.6.1 Primary outcome

COPD Assessment Test (CAT) The change in the CAT scores before (week 0) and after (week 12) the intervention is chosen as the primary outcome.

The scale evaluates and reflects the severity of COPD patients’ conditions through 8 items, including 3 indicators of clinical symptoms: cough, sputum, and chest tightness, 2 indicators of tolerance: exercise tolerance, daily activities (status of limited activities at home), and 3 indicators of life quality: sleep quality, energy, and mood (confidence in outings). The response values of each item are ranging from 0 to 5 (0 = no impairment). Response values for all 8 items will be summed up to obtain the total scores of (ranging from 0 to 40). Higher scores indicate a greater impact of the disease on the patient’s health and life (46): 0–9 is considered a low impact, 10–20 is considered a moderate impact, 21–30 is considered a high impact, and 31–40 is considered a very high impact (47). In addition, week 4, week 8 and the follow-up period (week 38, week 64) will also collect data on this scale’s scores (Table 1).

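### Baseline is entered as a random effect instead of a fixed covariate, and the model lacks the patient, visit and group-by-visit terms it would need if repeated visits were fitted together

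*Protocol article*

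**What the plan says.** Section 2.10 of the protocol article describes the model in detail. "Fixed effects will be set for analyzing groups, COPD subtypes and smoking index" gives the fixed part. The random part is "Random effects for sub-centers and baseline outcome measures, both including intercept". Tests use model-based covariance, and "the degree of freedom will use residual method". The same model is assigned to the effectiveness outcomes and to the microbiota, metabolite, immune-cell and cytokine measures. ANOVA is named for sensitivity analyses, without saying on which outcome.

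Sections 2.4.1 and 2.6.1 define the primary outcome as the change in CAT from week 0 to week 12, one value per patient. Section 2.6.1 adds: "In addition, week 4, week 8 and the follow-up period (week 38, week 64) will also collect data". Table 1 shows mMRC and SGRQ on the same schedule. The Discussion (section 3) says that the four-weekly data will be used to find out how long treatment needs to last, and that follow-up will show whether benefit persists.

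**The concern.** Two features of the model look wrong.

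- **Baseline is in the wrong part of the model.** As a random effect it can be read in two ways. It may be a grouping factor, so that patients who share a baseline score form a cluster. Or it may be a random slope with no fixed slope to centre it. The first ignores the order and spacing of the scores, and the second shrinks the slope towards zero. Neither is the usual baseline adjustment.
- **Nothing in the model represents the patient or the visit.** This is harmless with one row per patient. With several rows per patient, the rows would be treated as independent apart from centre and baseline, and the group coefficient would not refer to any one week.

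At stake are some precision in a small trial and, if visits are stacked, the validity of the test and the meaning of its estimate.

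**Working it through.** **Inputs from the protocol.** "Using a two-tailed test with type I error of 0.05 and power of 80%, a sample size of 32 cases per group is calculated"; "mean change in CAT scores of 5.0 for patients in the acupuncture group and 1.4 in the sham acupuncture group", a difference of 5.0 − 1.4 = 3.6; "with a maximum of 10% of participants allowed to drop out or disengage, for a required sample size of 36 cases per group". No SD and no between-visit correlation is given.

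**The plan's own figure.** The 32 per group cannot be reproduced without an SD, so the SD was solved for. By the normal formula, SD = 3.6 × √(32/2) / (1.960 + 0.842) = 14.4 / 2.802 = 5.14. With the exact t-test, SD 5.05 gives 80.2% power at 32 per group and 5.1 gives 79.4%. The dropout step reproduces: 32 / 0.9 = 35.6, rounded up to 36. An SD of about 5 is used below as an assumption.

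**Stacked visits, by formula.** Group is constant within a patient. With *m* visits, common correlation ρ and no patient effect, the true SE is √(1 + (m − 1)ρ) times the reported SE, and type I error is 2Φ(−1.96 / ratio).

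| m | ρ | SE ratio | Type I error |
|---|---|---|---|
| 3 | 0.3 | √1.6 = 1.26 | 0.121 |
| 3 | 0.5 | √2.0 = 1.41 | 0.166 |
| 3 | 0.7 | √2.4 = 1.55 | 0.206 |
| 5 | 0.3 | √2.2 = 1.48 | 0.186 |
| 5 | 0.5 | √3.0 = 1.73 | 0.258 |
| 5 | 0.7 | √3.8 = 1.95 | 0.315 |

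The formula leaves out the random baseline term, so the stated model was also simulated.

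**Simulation A.** No true effect, REML, model-based SE, residual df, 64 patients, 4 centres, SD 5, ρ = 0.5, 150 runs per row. Baseline is an integer score except where marked.

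| Data | Baseline term | Empirical SD | Mean SE | Type I error |
|---|---|---|---|---|
| Week 12 only | random, grouped by value | 1.378 | 1.322 | 0.073 |
| Week 12 only | random slope by centre | 1.339 | 1.286 | 0.060 |
| Week 12 only | fixed | 1.316 | 1.272 | 0.040 |
| 3 visits | random, grouped by value | 1.288 | 0.782 | 0.193 |
| 3 visits | random slope by centre | 1.012 | 0.737 | 0.173 |
| 3 visits | fixed, no patient effect | 1.194 | 0.730 | 0.220 |
| 3 visits | fixed, plus patient intercept | 1.165 | 1.060 | 0.073 |
| 3 visits, continuous baseline | random, grouped by value | 1.104 | 1.130 | 0.060 |
| 5 visits | random, grouped by value | 1.066 | 0.617 | 0.247 |
| 5 visits | random slope by centre | 1.043 | 0.570 | 0.300 |
| 5 visits | fixed, no patient effect | 1.085 | 0.561 | 0.287 |
| 5 visits | fixed, plus patient intercept | 1.062 | 0.987 | 0.067 |
| 5 visits, continuous baseline | random, grouped by value | 1.074 | 1.081 | 0.047 |

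Monte Carlo error of a rate is √(p(1 − p)/150): 0.018 at p = 0.05 and 0.035 at p = 0.25.

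**Simulation B.** Also 64 patients and 4 centres, with change SD 5.06, between-visit correlation 0.6 and 400 to 700 runs. Week 12 only: type I error 0.035, mean SE 1.25 against 1.19 for ANCOVA. Three visits: 0.151 (grouped by value) and 0.123 (slope by centre). Five visits: 0.252. Three visits with fixed baseline and a patient intercept: 0.053.

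**Precision at week 12.** The ratios to a fixed baseline are 1.378/1.316 = 1.05 and 1.339/1.316 = 1.02 in A, and 1.25/1.19 = 1.05 in B. Each empirical SD in A has a relative error of about 1/√300 = 6%, so the size is only indicative.

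**What the stacked coefficient targets.** Suppose the 3.6-point difference built up linearly as 1.2, 2.4 and 3.6 at weeks 4, 8 and 12. The coefficient would then target (1.2 + 2.4 + 3.6)/3 = 2.4. If 1.8 remained at weeks 38 and 64, the five-visit average would be 10.8/5 = 2.16.

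**The case against.** The primary outcome is a single change score per patient. Fitted to that, the model needs no visit term, a patient intercept could not be separated from the residual, and residual df do not count visits as patients. Section 2.10 never mentions stacking. The same model is assigned to the biological measures, which have only one post-baseline sample, and this points towards one row per patient. Weeks 4, 8, 38 and 64 could be analysed one at a time. An article may leave the layout of the data to the analysis plan, and an ANOVA sensitivity analysis is planned.

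Most of this stands. A reader might infer that the model misses the week-12 difference, or that the primary test runs at 12 to 32% type I error. The documents do not support either inference, because both require stacked visits.

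Two things remain. The placement of baseline is stated, not omitted, in a section that goes down to the iteration limit. And the time-course question in the Discussion cannot be answered by one fit without visit terms. The planned ANOVA does not settle which visits the main model uses.

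**Conclusion.** The concern holds in a limited form.

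- **On any reading,** baseline is misplaced. With week 12 alone the cost is an SE roughly 2 to 5% larger than with ANCOVA, under an assumed SD near 5. The week-12 difference is still estimated, with near-nominal type I error (0.035 to 0.073 across the simulations).
- **Only if visits are stacked,** the coefficient becomes an average over visits. Type I error for CAT is then about 12 to 21% with three visits and 19 to 32% with five, for assumed ρ of 0.3 to 0.7. Moving baseline to the fixed part does not cure this by itself (0.220 and 0.287 at ρ = 0.5); a within-patient term is also needed.
- **Exception.** For continuous outcomes with nearly unique baseline values, a baseline grouping factor acts as a patient intercept and the inflation largely disappears (0.060 and 0.047). This does not help CAT, an integer from 0 to 40, or mMRC, which has five grades.

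The SD, the correlation and the build-up of the effect are assumptions, because the protocol gives none of them.

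**What to change.** In section 2.10, move the baseline outcome to the fixed effects and state that the primary analysis is the group contrast in CAT at week 12. Either of two models will serve:

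- a week-12-only ANCOVA-type model with group, baseline, centre, COPD subtype and smoking index; or
- a repeated-measures model that adds visit, group-by-visit and a within-patient covariance (or patient intercept), with the week-12 contrast named as primary.

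For the treatment-duration and follow-up questions, use the repeated-measures form or separate models for each visit, and say which. The change is to wording only. The planned software can fit either model, and no new data are needed.
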